## Abstract

**Background:**

Unhealthy nutrition and lifestyle contribute to the worldwide rising prevalence of non-communicable diseases. This also accounts for the reproductive population, in which unhealthy behavior affects fertility and pregnancy outcome. Maternal smoking, alcohol consumption and inadequate folic acid supplement use are strongly associated with fetal complications as small for gestational age, premature birth and congenital malformations. In the Netherlands 83% of the perinatal mortality rate is due to these complications and is relatively high compared to other European countries. In order to reduce this prevalence rate, preconception care should be focused on the promotion of health of prospective parents by identification and intervention on modifiable nutrition and lifestyle risk factors. We developed the personal mHealth program ‘Smarter Pregnancy’ (Dutch version available on: https://www.slimmerzwanger.nl) to provide individual coaching and information to improve nutrition and lifestyle during the preconception period in order to improve health of the reproductive population and subsequent generations.

**Methods:**

Women between 18 and 45 years of age, and trying to conceive are eligible for inclusion in a randomized controlled trial. Participants are allocated either to a general population cohort or a subfertile (IVF/ICSI) population cohort. The intervention group receives personal online coaching based on the identified nutrition and lifestyle risk factors at baseline. Coaching comprises recipes, incentives, additional questions including feedback and text and e-mail messages, with a maximum of three per week. The control group only receives one recipe per week to maintain adherence to the program and prevent drop out. Screening questionnaires are send in both groups at 6, 12, 18, and 24 weeks of the program to monitor the change in the identified risk factors.

**Discussion:**

We expect to demonstrate that the mHealth program ‘Smarter Pregnancy’ can effectively improve nutrition and lifestyle in couples contemplating pregnancy. By the identification and improvement of modifiable nutrition and lifestyle risk factors on a large scale, both reproductive and pregnancy outcomes can be improved and subsequent perinatal morbidity and mortality rates are expected to be reduced. The current use and rapid development of mHealth applications offers new opportunities to reach and educate large populations, which can facilitate the implementation of preconception care.

**Trial registration:**

Dutch trial register: NTR4150. (Registered 19^th^ August 2013)

**Electronic supplementary material:**

The online version of this article (doi:10.1186/s12884-017-1228-5) contains supplementary material, which is available to authorized users.

## Background

Unhealthy nutrition and lifestyle, characterized by a high caloric intake and vitamin deficiencies, derange metabolic and endocrine pathways and are causing obesity which contributes to the development of non-communicable diseases (NCDs), such as cardiovascular and metabolic diseases [1, 2]. Although awareness of the impact of unhealthy nutrition and lifestyle is increasing, its prevalence remains very high, not only in general, but also in the reproductive population in which health consequences range from subfertility to congenital malformations or even perinatal death [3–7]. Most evidence is available on the detrimental impact of maternal smoking, alcohol consumption and inadequate folic acid supplement use, which are strongly associated with embryonic growth and small for gestational age (SGA) and congenital malformations [8–12]. Currently, several studies that focused on the adherence of maternal dietary patterns have shown the benefits of healthy foods such as fruits and vegetables on perinatal outcome [13, 14].

In the Netherlands, particularly in large cities such as Rotterdam, perinatal mortality rates and the prevalence of perinatal complications, such as SGA, premature birth and congenital malformations (also referred to as Big3 complications), is relatively high compared to other European countries [15–17]. In order to reduce these prevalence rates, preconception care (PCC) should be implemented, focused on the promotion of health and the identification of (modifiable) risk factors of prospective parents as well as the next generation [18–20].

In order to create awareness and to implement PCC on a large scale, new approaches need to be explored and (mobile) technologies can be used. Previously, we developed and implemented a preconception outpatient clinic tailored to improve nutrition and lifestyle of which the results were promising, i.e. 30% reduction of inadequate nutrition and lifestyle and a 65% increased chance of ongoing pregnancy after IVF treatment [4, 21]. However, this outpatient clinic could only provide PCC on a small scale due to the required expertise, time and costs. To overcome these barriers we have developed the personal mHealth coaching program ‘Smarter Pregnancy’ (Dutch version available on: www.slimmerzwanger.nl, English equivalent available on: https://www.smarterpregnancy.co.uk/research/), providing individual, tailored and continuous information on a large scale during 26 weeks. Previous studies have shown that women seek online information with regard to healthy nutrition and lifestyle which suggests that online interventions using mobile technology can be effective [22, 23]. Also, women embrace online anonymity to control and self-manage online information [24, 25]. Smarter Pregnancy identifies the most important risk factors regarding nutrition and lifestyle and subsequently provides tailored information and motivational coaching by text and e-mail messages [6].

We hypothesize that our mHealth program will effectively improve nutrition and lifestyle in couples contemplating pregnancy. Based on our previous studies and that of others we designed a randomized controlled trial (RCT) to study the effectiveness of “Smarter Pregnancy”, defined as a significant improvement of vegetable and fruit intake and folic acid supplement use, when started preconceptional [4, 6, 7, 21, 26]. This intervention can be considered as a primary prevention tool resulting in a reduction of Big-3 complications, perinatal morbidity and mortality in the short-term and NCDs in the long-term [2, 27, 28].

### Objectives

A randomized controlled trial is conducted in two independent populations, i.e. couples from the general population and couples undergoing IVF/ICSI treatment, to study whether unhealthy nutrition and lifestyle can be improved by the Smarter pregnancy coaching program as an intervention tool. Furthermore, we will determine whether couples will have a higher pregnancy rate and if their risk for Big3 complications can be reduced by improving nutrition and lifestyle.

#### Primary outcome

Improvement (percentage reduction) of unhealthy nutrition and lifestyle in women and men contemplating pregnancy or already pregnant, determined by using a dietary risk score (DRS), 24 weeks after starting the “Smarter Pregnancy” intervention.

#### Secondary outcomes

1) A reduction in smoking by women and men contemplating pregnancy; 2) pregnancy rates in couples; 3) birth prevalence rate of Big-3 complications in the entire study population; 4) cost-effectiveness of the Smarter Pregnancy intervention.

#### Tertiary outcomes

The influence of participation of men, pregnancy, age, low socioeconomic status on the primary outcome and 1) Improvement (defined as the percentage of reduction) of unhealthy nutrition and lifestyle 36 weeks after starting the “Smarter Pregnancy” intervention; 2) the compliance and reliability of “Smarter Pregnancy” among both women and men. To study the latter, we aim to determine the: 1) The percentage of the target group that meets all the inclusion criteria for the study, but does not participate; 2) The percentage of participants that is still participating after three months (compliance); 3) The prevalence and nature of technical problems.

## Design

### Eligibility

Women residing in the Netherlands who are between 18 and 45 years of age and contemplating pregnancy are considered eligible to be included in this study. To participate, women need to be in possession of a smartphone with Internet access. Women with insufficient knowledge or understanding of the Dutch language, women who are treated by a dietician to lose weight in the context of a fertility treatment, and women who have a specific diet (e.g. vegans) cannot participate in the study. Male partners are also invited to participate, but only if they meet the same criteria, except that there is no upper age limit for male participants.

### Recruitment, cohort composition and randomization

Women are invited to participate by a (health care) professional from their midwifery practice, children’s daycare, childhealth center, or hospital. Self-registration through the website is also possible. Potentially eligible participants are contacted after registration by one of the researchers to verify their eligibility, to provide more details and answer questions about “Smarter Pregnancy” and to confirm their registration.

Participants are allocated either in a general population cohort or the IVF/ICSI- (ART) population cohort, depending on whether they will receive fertility treatment. Randomization of the participants is stratified by cohort and per center of inclusion. For each stratum a permuted block design is used and programmed beforehand. Hereby, allocation concealment is ensured.

### Smarter pregnancy

The mHealth program Smarter Pregnancy was launched in 2012 and provides personal coaching, tailored on personal conditions, gender, nutrition and lifestyle in both women and men contemplating pregnancy. The program is based on nearly 30 years of research and expertise by our group on the influence of nutrition and lifestyle on reproduction and pregnancy course and outcome. We used elements of Prochaska and Diclemente’s transtheoretical model with a focus on the readiness for behavioral change, Bandura’s social cognitive theory for self-efficacy and Fogg’s behavior model to include triggers to motivate and increase the ability to change [29–31]. Features of the attitude, social influence, and self-efficacy (ASE) model for coaching are applied; aimed at the understanding and motives of people to engage in specific behavior [32].

### Intervention group

The content of the individual coaching is based on the baseline screening on personal conditions, nutrition and lifestyle and monitoring questionnaires at 6, 12, 18, and 24 weeks of the Smarter Pregnancy program. At these time points, participants are invited to complete a short, online questionnaire to monitor the change in their nutrition and lifestyle. Results from the questionnaires are compared with the previous results and shown on a personal online page to show a participant’s progress.

The tailored coaching includes a maximum of three interventions per week comprising short message service (SMS) text and email messages containing tips, recommendations, vouchers, seasonal recipes, and additional questions addressing behavior, pregnancy status, body mass index (BMI) or adequacy of the diet (Fig. 1, colored arrows above black arrows).

**Fig. 1 Fig1:**
[figure not shown]
Overview of the recruitment and composition of the multi-center study and both cohorts

The personal page also provides access to additional modules (i.e. applications) to support physical activity, an agenda to improve the compliance with hospital appointments and medicine adherence, and a module to monitor the safety of prescribed medication. A summary of all individual results can be obtained at any moment by the participant, and can be handed over or sent by email to the health care professional for further evaluation and support of preconception and antenatal care.

### Control group

Participants who are randomized in the control group will not receive personal coaching after the baseline screening. They do receive access to their personal page and will receive one seasonal recipe per week to maintain adherence and prevent drop out (Fig. 1, lower red arrows). At baseline as well as at 12 and 24 weeks, participants in the control group receive the monitoring questionnaire about nutrition and lifestyle, but without feedback on the results. Also, every 6 weeks the controls receive a request to adjust their pregnancy status if needed.

### Biomarker validation

To validate the self-administered questionnaires, we will analyze several blood biomarkers in a random sample of both study populations and both groups (intervention and control group). A team of qualified medical students will take blood samples at the participants home address or at the hospital. These blood samples will be taken on three time points (t = 0, 12 and 24 weeks) during the study; each time 20 ml will be collected. Samples are kept at −20° Celsius for a maximum time period of 4 h. Aliquots of residual blood will be stored at −80° Celsius for future research on DNA and epigenetics.

### Additional study questionnaires and follow-up

At baseline, for both the intervention and the control group additional information on social and demographic characteristics is obtained using an additional online study questionnaire implemented in the coaching program. The first follow-up study questionnaire will be send at 36 weeks, i.e. 12 weeks after the last screening moment (Fig. 2). One year after enrollment, participants receive their last study questionnaire, which consists of questions regarding medical and obstetric history, medication use, whether they became pregnant during enrollment and, if applicable, the pregnancy outcome.

**Fig. 2 Fig2:**
[figure not shown]
Overview of both the intervention and control group during their enrollment. The upper arrows pointing downwards depict the intervention group. The lower arrows pointing upwards depict the control group. All boxed icons depict aspects of the trial that account for all participants in both groups, i.e. baseline screening, screening questionnaires (at t = 12 and t = 24 weeks), additional questionnaires at baseline and 52 weeks, pregnancy status per 6 weeks and blood samples (see Additional file 1: SPIRIT-Table)

### Statistical considerations

Sample size calculations are based on our primary outcome measure (DRS). Based on our previous studies and the survey using Smarter Pregnancy, we expect a reduction of approximately 0.5 DRS points (based on a standard deviation of 2.7) in the intervention group compared to the control group. Considering alpha = 0.05 and power = 0.80 we will need to include a total of 916 women in our study (2 arms of 458 each). Due to expected drop outs of approximately 10%, we aim to include 1000 fertile (2 arms of 500 each) and 1000 subfertile women (2 arms of 500 each) in our study. For 50% of these women, we expect their male partner (*n* = 250 in each arm) to participate as well. Due to the lower SD (2.0) in men, with this sample size we are also able to demonstrate a reduction of at least a 0.5 DRS points in the male partners.

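### The claim that 0.5 DRS points can be shown in men treats 250 enrolled men per arm as if all were analysed; at about 10% loss, unadjusted power is about 75%

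*Protocol article*

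**What the plan says.** All the figures come from the Protocol article, Statistical considerations.

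- **Women, requirement.** The article expects a between-arm difference in the dietary risk score (DRS): "we expect a reduction of approximately 0.5 DRS points (based on a standard deviation of 2.7"). With "Considering alpha = 0.05 and power = 0.80", it concludes that "we will need to include a total of 916 women in our study (2 arms of 458 each").
- **Women, allowance for loss.** The target is then raised: "Due to expected drop outs of approximately 10%, we aim to include 1000 fertile (2 arms of 500 each"), with the same number for the subfertile cohort.
- **Men.** Half of these women are expected to bring a participating partner, which gives 250 men in each arm. "Due to the lower SD (2.0) in men", the article continues, "with this sample size we are also able to demonstrate a reduction of at least a 0.5 DRS points in the male partners".

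The section gives no power, dropout rate or evaluable number specific to men. Elsewhere, the primary outcome covers women and men at 24 weeks (Primary outcome), and the DRS of both sexes at baseline and 24 weeks enters the analysis (Statistical analysis).

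**The concern.** The women's figure is built in two steps: the number needed with data, then an increase for dropout. The men's figure skips the second step. It is a fraction of the women's enrolment target, which already includes the dropout allowance, and it is then used as the number analysed. Since 250 is almost exactly what 80% power needs at SD 2.0, there is no reserve to absorb any loss of men.

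Men are part of the primary outcome, and the article presents the ability to show 0.5 points in them as a property of the design. If the power is really in the mid-70s, the chance of missing a true 0.5-point effect in men is about one in four instead of one in five. Readers of a non-significant result in men should know that.

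**Working it through.** **Inputs (Statistical considerations unless noted)**

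- Difference 0.5 DRS points, for women and for men.
- SD 2.7 in women, 2.0 in men.
- Alpha 0.05 and power 0.80, stated in the women's calculation. Sidedness is not stated; two-sided is inferred because it reproduces 458.
- Men enrolled: 50% × 500 = 250 per arm in each cohort.
- Dropout about 10%, stated for the women's target. Applying it to men is an assumption.
- Cohorts taken separately: the Objectives section calls them independent populations, and each is given its own 500 per arm.

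**Step 1: reproduce the women's figure.** For two means, n per arm = 2 × [(1.96 + 0.8416) × SD / difference]².

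2 × (2.8016 × 2.7 / 0.5)² = 457.7, so 458 per arm. This matches the article, so its method is the plain two-sided, two-sample formula without baseline adjustment.

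**Step 2: same formula for men.** 2 × (2.8016 × 2.0 / 0.5)² = 251.2, so 252 men per arm with 24-week data.

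**Step 3: power and detectable difference for men.** Power = Φ(0.5 / [2.0 × √(2/n)] − 1.96). Difference detectable at 80% power = 2.8016 × 2.0 × √(2/n).

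| Men analysed per arm | Loss | Power, normal | Power, t-test | Detectable at 80% |
|---|---|---|---|---|
| 250 | none | 79.8% | 79.7% | 0.501 |
| 229 | 8.4% | 76.3% | 76.1% | 0.524 |
| 225 | 10% | 75.5% | 75.4% | 0.528 |

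The 8.4% row uses the loss implied by the women's own numbers: 1 − 458/500 = 0.084, and 250 × 0.916 = 229. As an example, for 225: 0.5 / (2.0 × √(2/225)) = 2.652; 2.652 − 1.96 = 0.692; Φ(0.692) = 0.755.

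**Step 4: what baseline adjustment could recover.** Suppose 2.0 is the SD of the unadjusted 24-week score, and let r be its correlation with baseline. The residual SD is then 2.0 × √(1 − r²), and the requirement falls to 251.2 × (1 − r²). Setting this equal to 225 gives r² = 1 − 225/251.2 = 0.104, so r ≈ 0.32, or about 0.33 with the t-test. Power at 225 per arm (normal approximation) for assumed values of r:

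- r = 0.10: 76.0%
- r = 0.20: 77.2%
- r = 0.30: 79.4%
- r = 0.35: 80.8%
- r = 0.50: 86.5%

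The article gives no value for r and does not say whether 2.0 is the SD of the score, of its change, or the residual SD after adjustment.

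**The case against.** The case on the other side has several parts.

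- **The 80% for men is implied.** This is so. Power of 0.80 appears only in the women's calculation. But the men's sentence follows from it as something the trial can also do, and 250 men return 79.8%, so 80% is the natural reading.
- **The 10% is given for women.** This stands as a caveat. A reader might infer that the plan itself expects 225 men to finish; it does not say so. The figure of 75% is conditional on carrying the rate across. The direction is not: any loss among men takes unadjusted power below 79.8%.
- **The planned model includes the baseline DRS.** This is the strongest objection. A modest correlation of about 0.33 would restore 80% if 2.0 is unadjusted. It is therefore tempting, but wrong, to conclude that the design cannot show 0.5 points in men. The text does not settle which SD is meant, and its own arithmetic uses no adjustment.
- **The inputs are rounded.** At 225 per arm, an SD of 1.95 gives 77.5% and 2.05 gives 73.3% (t-test), a spread about as large as the shortfall. The 250 is itself an expected uptake, since partners are only invited. This limits how exact the 75% can be, but it does not explain why men receive no dropout allowance.
- **The consequence is small.** The expected 95% confidence interval half-width goes from 1.96 × 2.0 × √(2/250) = 0.351 to 1.96 × 2.0 × √(2/225) = 0.370. That is fair, and it argues for a proportionate correction.
- **Pooling the cohorts would cure it.** With 450 men per arm, power would be about 96%. But the article sizes each cohort separately as an independent population.

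A reader might also extend the point to women, because 500 × 0.9 = 450 is below 458. Power at 450 is 79.3%, and with loss given only as approximately 10% this is rounding and no finding.

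**Conclusion.** The men's statement uses an enrolment count as an analysis count. On the article's own unadjusted formula it holds only with complete follow-up of men, which the article nowhere assumes. At about 10% loss, power for 0.5 points is about 75%, a shortfall of about 4.5 percentage points, and the difference detectable at 80% power is about 0.53 points. At 8.4% loss power is about 76%.

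These sizes rest on a two-sided alpha of 0.05, an 80% target carried over from the women's sentence, the women's dropout rate applied to men, separate cohorts, and no gain from baseline adjustment. The last assumption is the least certain. The shortfall is modest and would disappear with a baseline correlation of about 0.33 if 2.0 is an unadjusted SD. What remains is a stated design property, for a population named in the primary outcome, that its stated inputs do not deliver. It should be corrected.

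**What to change.** Revise the men's sentence in Statistical considerations in one of two ways.

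1. State that about 225 evaluable men per arm per cohort are expected after roughly 10% loss, giving about 75% power for 0.5 DRS points, or 80% power for about 0.53 points.
2. State that 2.0 is the unadjusted SD, give the assumed correlation between baseline and 24-week DRS with its source, and recompute the power for 225 men per arm with the baseline-adjusted model.

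The cost is one sentence. The first option makes the stated power slightly less favourable; the second requires a correlation, presumably from the group's earlier data. Neither changes enrolment, conduct or analysis. The women's figures can stay as they are.

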### Statistical analysis

A flowchart will be used to depict the total participants of each cohort and divided per group, subdivided per gender. Also, the amount of resigning participants will be shown per time point (6 weeks). General and baseline characteristics will be compared between groups and shown in a baseline table.

The primary analysis will be based on intention to treat (ITT). For men and women in both the intervention and the control group the DRS will be calculated at baseline and after 24 weeks and used for further analyses. This continuous outcome measure will be analyzed by the ‘difference in difference principle’ and used in a linear regression model, including the initial/baseline value of the DRS. Repeated measurements will be used to investigate the effects of the intervention over time and the interaction of the intervention with socio economic status, ethnicity and age. Chi-square analysis and ANCOVA will be used to study the effects of the intervention on the pregnancy outcome and Big-3 complications.

To measure the compliance and reliability of ‘Smarter pregnancy’ we will analyze the percentage of randomized women who fill in the questionnaire after 12 weeks of participation and the percentage of participants who experienced technical problems. Corresponding confidence intervals will be given.

The influence on the primary outcome of participation of men, if pregnancy occurred during participation, age and low socio economic status will be analyzed by including these variables and their interaction with both groups, one by one in the model which will be used for the primary outcome. If there is heterogeneity of the treatment effect, the effect will be determined per subgroup separately.

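### Randomisation is stratified by cohort and centre, but the primary DRS regression as described names neither factor and does not say that it is fitted per cohort

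*Protocol article*

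**What the plan says.** In the protocol article, the section on recruitment, cohort composition and randomisation states: "Randomization of the participants is stratified by cohort and per center of inclusion". It adds: "For each stratum a permuted block design is used and programmed beforehand". Block size and number of centres are not given.

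The section Statistical analysis applies a difference-in-difference principle to the DRS at baseline and 24 weeks, "used in a linear regression model, including the initial/baseline value of the DRS". It then lists variables to be added to this model one at a time with their interaction with arm: male participation, pregnancy during the trial, age and low socioeconomic status. The repeated-measures analysis names socioeconomic status, ethnicity and age. Centre and cohort appear in none of these lists. Cohort is mentioned only for the flowchart.

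Elsewhere the cohorts are kept apart. Under Objectives: "A randomized controlled trial is conducted in two independent populations, i.e. couples from the general population and couples undergoing IVF/ICSI treatment". Under Statistical considerations, 916 women (458 per arm) are required, and the recruitment target is set per cohort: "we aim to include 1000 fertile (2 arms of 500 each) and 1000 subfertile women (2 arms of 500 each) in our study".

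**The concern.** Permuted blocks within strata balance the arms on whatever the strata predict. The treatment estimate then no longer varies because of stratum differences. A linear model without the strata still counts those differences as residual error, so its standard error exceeds the true sampling variability. Intervals come out too wide and the test runs below its nominal level. This happens only to the extent that the strata predict the outcome after baseline DRS.

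The second part is clarity. The design reads as two trials of 1000 women each, but the analysis section does not say whether the primary result is one estimate or two. Cohort is also missing from the list of effect modifiers, so a pooled fit of the model as described would not examine whether the effect differs between the general and IVF/ICSI populations. If this is left open, the choice between pooled and per-cohort results could be made after the data are seen.

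**Working it through.** **Inputs from the article (Statistical considerations):** difference 0.5 DRS points, SD 2.7, alpha 0.05, power 0.80, 500 women per arm per cohort, dropout about 10%. Completers per arm per cohort: 500 × 0.9 = 450.

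**Input not in the article:** R², the share of residual DRS variance explained by the strata after baseline DRS. Assumed range 0 to 10%.

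**1. The plan's own figure.** n per arm = 2 × 2.7² × (1.960 + 0.842)² / 0.5² = 457.7, so 458 per arm and 916 in total. This reproduces the stated number with a two-sided test. It uses the full SD of 2.7, with no reduction for baseline DRS or any other covariate.

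**2. Starting point.** With 450 per arm, SE = 2.7 × √(2/450) = 0.180, and power = Φ(0.5/0.180 − 1.960) = 79.3%. The shortfall of under one point from 80% comes from rounding the dropout allowance and is unrelated to the strata.

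**3. Effect of leaving out the strata.** With balanced strata the true sampling SE is 0.180 × √(1 − R²), while the unadjusted model reports about 0.180. Hence:

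- SE inflation = 1/√(1 − R²) − 1
- actual type I error = 2 × [1 − Φ(1.960/√(1 − R²))]
- unadjusted power = Φ((0.5/0.180 − 1.960)/√(1 − R²))
- adjusted power = Φ(0.5/(0.180 × √(1 − R²)) − 1.960)

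| R² (assumed) | SE too wide by | Type I error | Power, unadjusted | Power, adjusted | Forgone (points) |
|---|---|---|---|---|---|
| 0% | 0% | 5.0% | 79.3% | 79.3% | 0 |
| 1% | 0.5% | 4.9% | 79.4% | 79.7% | 0.3 |
| 2% | 1.0% | 4.8% | 79.6% | 80.1% | 0.6 |
| 5% | 2.6% | 4.4% | 79.9% | 81.3% | 1.4 |
| 10% | 5.4% | 3.9% | 80.6% | 83.4% | 2.8 |

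Setting adjusted power simply against the 79.3% in step 2 gives at most 83.4 − 79.3 = 4.1 points. The table is the closer comparison, because balance also makes the unadjusted estimate itself more stable.

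**4. Simulation check.** Assumed: 900 women, 10 centres, blocks of 4, 4000 repetitions. With 10% of residual variance between centres, the unadjusted model reported an SE of 0.179 against an empirical SE of about 0.172. Type I error was about 4.0% (4.7% adjusted), and power 80.4% (83.1% adjusted). With 2%, power was 79.4% against 80.2%. With 0% there was no difference.

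**5. With credit for baseline DRS.** If baseline and 24-week DRS correlate 0.5 (assumed), the residual SD is 2.7 × √0.75 = 2.34. Power at R² = 0 is 89.4%. With strata in the model it is 89.7, 90.0, 90.8 and 92.2% at R² of 1, 2, 5 and 10%.

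**6. If the cohorts were pooled.** With about 900 completers per arm, power for 0.5 points is 97.5% before any adjustment, so lost power would hardly matter. What a pooled model without cohort terms would cost is the separate answer for each population.

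**The case against.** **The covariate list may be complete elsewhere.** The article says that the model includes baseline DRS, not that baseline DRS is the sole covariate. It condenses a fuller protocol, and an analysis plan may add centre. This stands, so a reader should not infer that the trial will certainly be analysed without the strata. Even so, the article describes the model in some detail and names several variables to be added; the two factors that the design controlled are not among them.

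**Cohort is largely settled by context.** The objectives call the cohorts independent populations, each has its own target of 1000 women, and only the Big-3 outcome is explicitly taken over the entire study population. No passage proposes pooling the DRS. This stands too: separate analysis is the likelier reading, and centre is then the only stratifier left out. What remains is that the analysis section does not say so.

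**No power is lost against the plan.** It is tempting to conclude that the trial is underpowered or that its standard errors are wrong. The documents do not support this. The 916 was computed from the unreduced SD, so omitting centre only forgoes a possible gain, and any error is conservative.

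**The effect of centre is unknown.** The article reports no between-centre variance. For a self-reported score collected through the same online program everywhere, the centre effect after baseline adjustment could be close to zero. This stands, and is why the range above starts at 0%. On the other side, recruitment runs through midwifery practices, daycare, child health centres, hospitals and the website, so some difference between sources is plausible.

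**Conclusion.** The point holds as a modest one about efficiency and clarity. Randomisation is stratified by cohort and centre; the primary regression as described names only baseline DRS as a covariate and does not state that it is fitted per cohort.

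The size depends wholly on an assumption: the share of residual variance attributable to centre. Over 0 to 10%, the largest effects are a standard error 5.4% too wide, a type I error of 3.9%, and about 3 points of attainable power forgone at 450 per arm (4 on the simplest comparison). At 0% nothing changes. The treatment estimate is not biased, the type I error is not inflated, and the planned 80% is not undercut. The analysis as described would be valid. A claim that its standard errors are certainly too wide would go beyond what the article supports.

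**What to change.** State in the analysis section that:

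- the primary model is fitted within each cohort, with arm, baseline DRS and centre of inclusion as covariates, small centres being pooled by a rule set in advance, with a stated category for self-registrations through the website;
- any pooled analysis includes cohort and an arm-by-cohort term;
- the repeated-measures model uses the same strata.

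The cost is a few lines of wording. Stratum is needed to randomise each participant, so no new data are collected, and the sample size does not change. If the full protocol or analysis plan already contains these terms, it is enough to confirm this. The wording should be settled before outcome data are seen by arm, so that pooled or separate reporting is not chosen afterwards.
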